## Abstract

**Introduction:**

Forensic mental health care is hampered by lack of evidence-based treatments. The Swedish forensic mental health population consists of patients suffering from severe illnesses such as schizophrenia and bipolar disorders, similar to populations in international studies. Illness Management and Recovery (IMR) is an intervention for patients with serious mental illness, based on psychoeducational, cognitive-behavioral and motivational components. The purpose is to strengthen participants’ illness management skills and recovery.

**Objective:**

To test effectiveness of IMR within forensic mental health by comparing it to treatment as usual.

**Method:**

This is a cluster-randomized controlled trial. Patients in forensic mental health inpatient units are randomized to an active (IMR) or a control condition (treatment as usual). Clustering of patients is based on ward-units where inpatients are admitted. Patients in the active condition receive two group and one individual IMR sessions per week. The treatment phase is estimated to last nine months. Outcomes include illness related disability, illness management skills, sense of recovery, hope, mental health and security related problems. Outcomes are measured at baseline, four months into treatment, at treatment completion and at three months follow-up. Staff experiences of implementing IMR will be explored by a self-report measure and semi-structured interview based on Normalization Process Theory.

**Ethics and dissemination:**

The study is approved by the Swedish Ethical Review Authority (Registration No. 2020–02046). Participation will be voluntary based on written informed consent. Results will be disseminated through peer-reviewed articles and conferences. The study is registered in the US registry of clinical trials (NCT04695132).

## Introduction

1

Previous research has highlighted difficulties associated with treating criminal offenders suffering from serious mental illness. One fundamental aspect of forensic mental health care is that successful care does not only mean alleviating effects of mental illness, but also include minimizing risk of criminal recidivism. In addition to this, forensic mental health patients often suffer from psychiatric comorbidity and behavioral or lifestyle-associated problems that complicate treatment [[1], [2], [3]]. Furthermore, the compulsory nature of care complicates caregiver-caretaker relationships [4,5]. Overall, there is currently a paucity of knowledge guiding efforts to address needs of forensic mental health patients [1,6]. Considering the suffering associated with severe mental illnesses and the ramifications criminal re-offense have for society, this is an area in need of attention.

In a Swedish context, official data indicate that a majority of patients in forensic mental health services suffer from a schizophrenia spectrum disorder or a bipolar syndrome. Psychiatric comorbidity is common [46]. Furthermore, several governmental reviews conclude that scientific support for non-pharmacological interventions is highly unsatisfactory. These reviews also point to a large degree of heterogeneity in care provided at different in-patient forensic mental health facilities. One common practice is to import interventions from non-forensic psychiatry. However, translatability of interventions from a non-forensic context cannot be taken for granted and studying treatment effects specifically in forensic mental health populations is recommended [8,44]. With this in mind, we aim to study the effectiveness of a psychosocial treatment program, Illness Management and Recovery (IMR), within forensic mental health in-patient care. IMR was designed for individuals suffering from severe mental health problems [[9], [41]]. Previous research has focused on non-forensic populations, suffering mainly from schizophrenia spectrum disorders but also including patients with other syndromes (e.g. [[11], [12], [40]]). In Sweden, psychosocial treatments such as IMR, are strongly recommended in clinical guidelines for treatment of patients with schizophrenia spectrum disorders [45]. Given the aforementioned clinical characteristics of the forensic population, it is hardly surprising that IMR has started to proliferate as a treatment method within Swedish forensic inpatient clinics. Two of the authors of this study (PA & KS) have conducted a smaller pilot study of IMR (data not yet published) at a Swedish forensic clinic. However, that study focused on feasibility and acceptability, and to our knowledge, no study focusing on effects of IMR on forensic inpatients in Sweden or elsewhere has yet been published. With this in mind, we plan to evaluate the effectiveness of IMR by conducting a multi-center cluster randomized study in forensic inpatient psychiatry.

The two main objectives are:1.To evaluate whether forensic patients receiving IMR show improvements on outcomes such as functional impairment, illness management ability, subjective recovery, sense of hope, and/or self-experienced functional status, when compared to a control group receiving treatment as usual.2.To evaluate to what extent the presence of background risk markers for criminal recidivism and/or the functional status of participants in the treatment group moderate effects of IMR on treatment outcome measures.

In addition, a secondary objective is:3.To explore how staff working with IMR experience the process of implementing the treatment.

## Methods

2

The overall study design (described in further detail below and outlined in Fig. 1) is a cluster randomized trial conducted within inpatient forensic psychiatric clinics in Sweden. A clinic participating in the trial will nominate an even number of wards, which is the clusters of participating patients (conditional on them giving informed consent) that will be randomized to either a control or an active condition. Participants in the control condition will receive treatment as usual, whilst participants in the active condition receive IMR. Outcome measurements will be taken at four time points, baseline before treatment, four months into treatment, at treatment completion and at three months after treatment completion.

**Figure 1 fig1:**
[figure not shown]
Overview of study plan and timetable.

In addition to this, a mixed methods approach will be used to explore the experiences of staff delivering the IMR-treatment. This part of the study will be based on the framework postulated in Normalization Process Theory [13]. At three time-points, after completion of training, three months and twelve months after treatment commencement, staff will answer a questionnaire pertaining to implementation processes and, during the latter two assessment points, participate in semi-structured interviews regarding their experiences working with IMR.

### Settings of the study

2.1

The planned study will be conducted within in-patient forensic mental health facilities in Sweden. These facilities are tasked with providing court mandated compulsory forensic mental health care for individuals convicted of crimes who have been found to suffer from serious mental illness during the perpetration of their offense and at the time of a subsequent forensic mental health investigation. On the basis of these criteria, a court can convict an individual to compulsory mental health care rather than a traditional prison sentence [43]. In general, a forensic mental health inpatient facility in Sweden is structured around different ward units where patients live and receive care. The typical treatment process usually starts on an inpatient basis but can later on be converted to outpatient treatment. Treatment typically spans several years and thus, most commonly an individual sentenced to forensic mental health care within the Swedish system will spend a substantial time with the in-patient ward as their main living environment [14]. Previous studies have shown that the daily life of patients at these wards are to a large extent characterized by unstructured and unplanned activities, rather than treatment per se [15].

### Design

2.2

The project will be conducted with a cluster randomized study design. Each participating forensic mental health in-patient facility will nominate an even number of wards (i.e. clusters of patients), which will then be randomized to either the active (IMR) or control condition (treatment as usual). Randomization of clusters to condition will be matched, in the sense that each participating in-patient facility will have the same number of clusters within the two conditions (e.g. if four wards take part in the study at one facility, two wards will be randomized to each condition). Recruitment of new participating clusters of patients will take place continually until the desired sample size is reached. Assessments of patient outcome measures take place during four different time-points including baseline measurements.

In addition to the patient focused research, the study also aims to explore how staff implementing IMR experience working with the treatment method. This will be done in a mixed-methods fashion, based on the theoretical framework stipulated in Normalization Process Theory [[13], [42]]. Staff working at wards where IMR is implemented will be asked to complete a questionnaire pertaining to aspects of working with the intervention and queried about the same topic in more in-depth qualitative interviews. Data collection from staff will take place at three time-points during the study.

More details on the specifics of data collection is described below, under the heading “Measurement methods”.

#### Participants and recruitment

2.2.1

We aim to include patients from several forensic mental health inpatient facilities in Sweden. Thus, recruitment will start with approaching the management at the forensic mental health inpatient facility, informing them about the contents of the study and inquiring about their interest in participating. If the decision is made on the clinic level to participate in the study, the representatives of the inpatient facility will be asked to nominate an even number of wards that are considered as comparable to each other as possible. These wards are the clusters of patients that will be randomized to either of the two study conditions. An equal number of wards per inpatient facility will be randomized to either one of the two conditions. In practice, this means that a necessary criterion for each in-patient facility participating in the study is that they have at least two different wards that are considered equal enough in terms of structure and patient characteristics to be comparable to each other. We aim to recruit twelve wards (clusters) for the study (six in each condition) and estimate that a total of 80 patients, 40 in each condition, consent to study participation. To achieve this, we aim to include 4–6 forensic inpatient clinics in the study.

Prior to randomization of a ward to a specific condition, the patients to subsequently be approached for participation in the study will be identified in cooperation with the clinical team according to the inclusion and exclusion criteria delineated below. After randomization patients fulfilling inclusion criteria at these wards will then be informed about the study and asked for written consent regarding their participation. Recruitment of patients at each ward unit will take place during a time limited window of approximately 3–4 weeks after randomization of the ward unit, before IMR treatment start at wards randomized to the active condition. Given the aforementioned lack of evidence-based interventions in forensic mental health care, we would consider even small effect sizes to be of relevance. With that in mind, we would have preferred a larger sample size to have a sufficiently high probability of discovering such effects. A power calculation conducted in R version 4.1.2. indicated that a total of 228 patients (19 in each cluster) would be needed to achieve 80% power to detect a true effect size of .4, if a small intercluster correlation was presumed. However, it should be noted that some studies of the treatment outcome of IMR have reported substantially higher effect sizes than 0.4 [[16], [40]].

However, the selection of our planned sample size has been made based on a trade-off between a desire for statistical power and pragmatic considerations of what is feasible in a situation of limited time and resources. Furthermore, our study can hopefully be a part of data underlying future meta-analytic studies of the efficacy of treatments within the forensic inpatient context.

In addition to patients participating in the study, staff administering IMR-treatment to patients will also be recruited as participants to the study. These staff participants will answer questions pertaining to their experiences of implementing the intervention. Staff participants will only be recruited from the wards where IMR is implemented. Recruitment of staff participants will take place after the end of staff training prior to treatment commencement. The specific composition of this sample is dependent upon the organization of the wards participating in the study, but it is expected that this will mainly consist of nurses and auxiliary staff. More in-depth inclusion and exclusion criteria both for patient and staff participants are defined below.

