#### Patient inclusion criteria

2.2.2

1.The patient is sentenced to in-patient forensic mental health care, in accordance with the Swedish judicial framework. In practice, this means that they have committed a crime warranting incarceration and that they have been found to suffer from serious mental illness in a forensic psychiatric evaluation.2.The treating psychiatrist and treatment team at each ward must approve of participation before the potentially participating patient is given information on the study. They will be instructed to base this approval on the basis of whether or not this patient can participate in IMR and is capable of giving informed consent. Examples of such factors rendering informed consent and thus participation not possible include presence of severe active psychotic symptomatology or severe intellectual impairment. The treating psychiatrist and treatment team will have ultimate veto rights if they for some other reason think that the participation of a patient in the project is not advisable on ethical grounds or because of mental health considerations.

We do not require that study participants fulfill any specific diagnostic criteria. Given that a large majority of patients within the Swedish forensic mental health services suffers from either a schizophrenia spectrum or bipolar disorder we consider it highly likely that a majority of our sample will present these disorders as their main diagnosis. However, it is also likely that some of the patients in our sample will have autism or mild intellectual impairment as their main diagnosis. This is in line with previous research on IMR, where a majority of patients included has suffered from either schizophrenia spectrum or bipolar disorders, and a minority of participants has suffered from other forms of mental illness (see for example [11,12,16]).

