#### Clinician assessed functional status

2.3.4

To further address the second of our main objectives, the functional status of participants in the active group will also be assessed, with anamnestic measures of functional status as well as a shorter neuropsychological test. The background measures pertaining to functional status are focused on historical role achievement/fulfillment. These include information on how the participants have earned an income before admission into forensic services, what their living condition was, their frequency of social contacts, educational attainment and relationship status. During the first assessment of the outcome measures (before treatment commencement) the participants will also complete a short neuropsychological test called the Zoo map, which is a subtest from the Behavioral Assessment of Dysexecutive Syndrome (BADS). The Zoo map subtest is designed to measure the ability to plan and monitor one's performance and compliance with pre-specified rules [20]. The person taking the test is tasked with drawing a route throughout a zoo, whilst complying with certain rules of how the route can be designed. Earlier research has shown that persons suffering from schizophrenia show impairments in this test, when compared to healthy controls [21]. Differences between persons suffering from schizophrenia with either acute symptomatology or in a more stable phase of disease progression have also been demonstrated [22]. In addition to this, participants will also be asked to rate their own performance, by answering four questions on a four-point scale. We expect that the administration of the Zoo test will add 5–10 min to the first assessment of outcome measures.

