Clinician's rating.1.Mental health and security related problems

To assess the participant's mental health and the extent of security related problems affecting them, the Health of the Nation Outcome Scale-Secure version (HoNOS-S) [30,31] will be used. This is a questionnaire consisting of 19 items rated by a clinician on a five-point scale. Twelve clinical items assess the extent of the patient problems in four areas: behavior, function, symptoms and social adaption. In addition to the twelve clinical items in the original version, the secure version of HoNOS [31] also contain seven items that focus on the need for special security measures in conjunction with the care provided for the patient rated. In this project, the participants treating psychiatrists will be asked to answer this questionnaire. The HoNOS-S administered at treatment completion is the second primary outcome measure in the study.2.Level of illness-related disability

In addition to the interview version of WHODAS 2.0, the 36-item proxy-administered version of WHODAS 2.0 will be used. In this version an informant with good knowledge of the person assessed is asked to answer the same questions posed in the interview version of WHODAS 2.0, with necessary revisions to wording made to adapt it to the third person perspective of the proxy respondent [23]. This scale will be answered by a member of the forensic mental health staff with good knowledge of the participant.3.Illness management skill and sense of recovery

Similar to WHODAS, IMRs also exist in a proxy-answered version. This version of the scale consists of the same number of items (15) answered on the same five-point scale as the self-report version of the questionnaire [26]. The same proxy-respondent answering WHODAS will be asked to answer the proxy-version of IMRs.

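### Consent, and by inference baseline measurement, come after the wards are randomised, so who enters the trial can differ by arm even though the list of eligible patients is drawn up beforehand

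*Protocol article*

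**What the plan says.** Only the protocol article is at hand. Section 2.2.1 sets the order of steps.

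- **Listing comes first:** "Prior to randomization of a ward to a specific condition, the patients to subsequently be approached for participation in the study will be identified". This is done with the clinical team, against the inclusion and exclusion criteria.
- **Information and consent come second:** "After randomization patients fulfilling inclusion criteria at these wards will then be informed about the study and asked for written consent regarding their participation".
- **The window** is given as follows: "time limited window of approximately 3–4 weeks after randomization of the ward unit, before IMR treatment start at wards randomized to the active condition".

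Section 2.2.2 (Patient inclusion criteria) adds a gatekeeping step within the second inclusion criterion: "The treating psychiatrist and treatment team at each ward must approve of participation before the potentially participating patient is given information on the study". Approval rests on whether the patient can take part in IMR and can give informed consent. The team also "will have ultimate veto rights if they for some other reason think that the participation of a patient in the project is not advisable"; the reasons named are ethics and mental health. Neither step is dated relative to randomisation in that section.

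Baseline is placed before treatment (section 2, Methods) and is not placed before randomisation. Section 2.3.4 says: "During the first assessment of the outcome measures (before treatment commencement) the participants will also complete a short neuropsychological test". For HoNOS-S, one of the two primary outcomes, section 2.3.5 says: "In this project, the participants treating psychiatrists will be asked to answer this questionnaire". The proxy versions of WHODAS and IMRs are answered by a member of the forensic staff.

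The analysis of the primary outcomes is by intention to treat (section 2.4). The article describes no masking of patients, recruiters or raters.

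**The concern.** Randomising wards balances, on average, the patients who were on the list. It does not balance the subset who agree to take part once the ward's arm is set. The analysed set forms at consent, so intention to treat starts too late to protect the comparison.

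The two invitations differ. On an active ward the patient takes on two group sessions and one individual session a week for about nine months (2.2.4). On a control ward the patient takes on assessments, with IMR offered after the study if it is found more effective and the patient is still an inpatient (2.2.5). Willingness to accept the first plausibly depends on motivation, insight and functioning, which lie close to what the trial measures. The resulting bias could go either way.

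A second route runs through the baseline. If treating psychiatrists and ward staff know the arm when they give the baseline ratings, those ratings can differ by arm before treatment starts, and the time-by-treatment term in the planned mixed model uses them.

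The authors say that even small effects would be relevant, so a modest bias matters. The limitations discussed in section 4 do not include this one.

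**Working it through.** **Step 1: order of events.** Participation is conditional on consent (section 2), and consent follows ward randomisation (2.2.1). A patient who has not consented cannot be assessed for the study. Baseline therefore follows randomisation by inference; no sentence says so outright. That allocation is known at that point is also inferred, from open ward-level delivery, staff training before treatment starts on active wards, and the absence of any stated concealment.

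**Step 2: the planning effect used as a yardstick.** Section 2.2.1 gives 228 patients (19 in each of 12 wards) for 80% power at an effect of 0.4 with a small intercluster correlation. The value of that correlation (ICC) and the alpha are not stated; I assume a two-sided alpha of 0.05.

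- Per arm without clustering: 2 × (1.960 + 0.842)² / 0.4² = 98.1.
- Design effect at ICC 0.009: 1 + 18 × 0.009 = 1.162.
- 98.1 × 1.162 = 114.0 per arm, or 228 in total.

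The figure reproduces under a normal approximation with an ICC of about 0.01. The order of consent does not change it.

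**Step 3: shift from differential consent.** The inputs here are assumed, since the article gives no consent rates. Let consent be decided by a standard normal trait exceeding a cut-off, with proportion p consenting. The mean trait among consenters is φ(z_p)/p.

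| p | φ(z_p) | φ(z_p)/p |
|---|---|---|
| 0.60 | 0.3863 | 0.644 |
| 0.80 | 0.2800 | 0.350 |
| 0.90 | 0.1755 | 0.195 |

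The shift in the arm difference with no treatment effect is r × (difference in means), where r is the correlation of the trait with outcome.

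- 80% v 60%: 0.644 − 0.350 = 0.294. Times 0.3 is 0.088; times 0.5 is 0.147. That is 22–37% of 0.4.
- 90% v 60%: 0.644 − 0.195 = 0.449. Times 0.3 is 0.135; times 0.5 is 0.224.

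**Step 4: why this is an upper bound.** The formula has every consenter above every refuser on the trait. If consent correlates only ρ with the trait, multiply by ρ. At ρ = 0.5 the 80% v 60% case becomes 0.044–0.073 SD, or 11–18% of 0.4. Any part of the shift already present at baseline would be reduced further by baseline adjustment.

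**Step 5: effect on false positives.** Take 80 patients, 12 wards and an assumed ICC of 0.01. The standard error in SD units is √(2 × [1 + (80/12 − 1) × 0.01] / 40) = 0.230. Under a normal approximation, a nominal two-sided 5% test becomes:

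- about 7–10% for a shift of 0.088–0.147 SD;
- about 5–6% for a shift of 0.044–0.073 SD.

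The ICC matters little: over 0 to 0.05, the 0.147 SD case ranges from 9% to 10%.

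**The case against.** **Existing safeguards.** The list is fixed before randomisation, wards are nominated as comparable and balanced within facility, and the window is short. These do limit staff choosing whom to approach. They do not touch the patient's own decision to accept or refuse.

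**The invitations are less different than they look.** Controls may be offered IMR later, so interest in IMR can motivate consent in both arms. This stands as a softening. The offer is conditional and deferred, while the active-arm commitment is immediate.

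**The mixed model handles baseline differences.** In part it does: a stable level difference largely drops out of a time-by-treatment interaction. It does not drop out where the trait predicts change, as motivation might, and the planned t-tests at each time-point carry it through unadjusted.

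**Raters will know the arm at the end anyway.** True. The primary outcomes are at treatment completion, so reordering protects only the baseline ratings.

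**Stronger readings.** A reader might infer that the team can veto patients after learning the ward's arm. The text does not establish this. Approval and veto sit inside an inclusion criterion, and section 2.2.1 applies the criteria before randomisation; section 2.2.2 requires approval only before information is given. The timing is ambiguous. A reader might also take it as stated that baseline raters know the allocation. That is a strong inference from the order of steps and is not written in the article.

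**Conclusion.** The point holds for the order of consent. The article explicitly places information and consent after ward randomisation, describes no concealment, and so lets the analysed set form after allocation. Neither intention to treat nor the mixed model can fully repair arm-dependent consent. That baseline also follows allocation is inferred, but the inference is strong.

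The size is unknown. The 0.09–0.15 SD is a ceiling for one assumed scenario (80% v 60% consent decided wholly by the trait, r of 0.3–0.5, no baseline adjustment), and 0.04–0.07 SD is the figure with a looser link between trait and consent. If consent rates and reasons turn out alike in the two arms, the selection bias vanishes. The documents do not support saying that the trial will be biased by a given amount, or that vetoes will be used selectively. The change is worth making because it mainly reorders steps already planned.

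**What to change.** 1. At each facility, complete team approval, consent and all baseline measures on every nominated ward, and then randomise the wards. If randomisation must come earlier, keep the allocation sealed from ward staff, psychiatrists, recruiters and patients until the last baseline at that facility is in.
2. Reconcile sections 2.2.1 and 2.2.2 on when the team's approval and veto apply relative to randomisation. The veto is an ethical and mental-health safeguard and should not be restricted; what is needed is a statement of its timing and a record of its use.
3. Report the numbers listed, vetoed, approached and consenting, by arm.

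**Cost.** The planned sample size is unchanged. The start of staff training and treatment may slip by up to 3–4 weeks per facility. Wards are recruited continually (2.2), so facilities not yet randomised could adopt the new order even if others have started. For those already randomised, item 3 still applies.
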